#### Adolescents

We aim to enroll a minimum of 1300 adolescent participants. Eligible adolescents must (1) present for an annual well visit with a participating clinician in either study arm, (2) be aged 14 to 17 years at the time of their well visit, (3) report past 12-month alcohol use or past 12-month riding risk, and (4) have a smartphone and be willing to share their mobile phone number with the study team. We chose the minimum age of 14 years because there is low prevalence of prior alcohol use among younger adolescents (<5% of adolescents aged 12-13 years in our prior studies reported past 12-month drinking [[name], unpublished data, 2019]). In addition, to be considered fully enrolled, all adolescents must complete the previsit survey before seeing their clinician, as well as the CRAFFT screen for those scheduled to see a clinician in the intervention arm. Adolescents must be willing and able to complete monthly surveys for 12 months after their well visit.

Adolescent patients must not be (1) in foster care, (2) in college or trade school at the time of their well visit, (3) currently receiving counseling or treatment for a substance use concern from a specialty clinician, or (4) perceived by their clinician to be inappropriate for the study (eg, due to neurodevelopmental delays or another medical priority at the time of visit).

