We calculated the adolescent patient sample size by applying recruitment and retention rates, alcohol use and riding risk prevalence rates, intervention effect sizes, a within-clinician clustering design effect (0.90), and the clinician intraclass correlation coefficient for HED (0.008) seen in our pilot study [22]. We estimated a 37% past 12-month drinking prevalence rate, 28% riding risk prevalence rate among adolescents with past 12-month drinking, and a 5.8% riding risk rate among those with no past 12-month drinking. The 37% past 12-month drinking prevalence rate is similar to the 36.1% prevalence rate found on the 2018 Monitoring the Future Survey [42]. We applied slightly more conservative rates of participation (80% vs 82%) and retention (70% vs 75%) than those found in our pilot study to ensure that we achieve a sample size with sufficient power. With α set at ≤.05 and β at ≥.80, our power calculation indicated that a minimum analysis sample size of 888 participants with 12-month follow-up data would provide 86% power to detect an effect size of ≥20% in our primary outcome measure of HED. Applying the conservative estimate of 70% retention at 12 months, we need to recruit a minimum of 1268 participants. Thus, we estimate needing approximately 4200 adolescents to complete the eligibility survey, with 1600 (40% of those screened) meeting eligibility criteria, and 1300 (80% of those eligible) enrolling. To enroll this sample, we anticipate enrolling an average of 40 patients per clinician among up to 40 clinicians completing the study.

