#### Outcome Measures

A detailed listing of study outcome measures, their reference sources where applicable, and time points of data collection is presented in Table 2, and thus they are only briefly described here. These measures are also reported in the ClinicalTrials.gov registry.

Our primary outcome measure is past 90-day HED, as reported by adolescents during the 12-month follow-up period, among adolescents who report past 12-month drinking at baseline. HED is defined using the age- and sex-specific cut points recommended by the NIAAA: ≥3 drinks on a single occasion for youth assigned female at birth who are aged 14 to 17 years, ≥4 drinks for youth assigned male at birth who are aged 14 to 15 years, and ≥5 drinks for youth assigned male at birth who are aged 16 to 17 years [68]. Our secondary outcome measure is any past 90-day riding with a driver who was substance impaired (who used alcohol, cannabis, or another drug) or driving while substance impaired. The exploratory outcomes of interest include past 90-day days of use of other commonly used substances among adolescents (ie, nicotine and cannabis) and experience of negative consequences associated with alcohol use (eg, missing school or work and getting into trouble at school, home, or work). In addition, we will explore the following intermediate outcome measures as hypothesized effect mediators: (1) report of readiness to reduce or stop alcohol use using a readiness ruler [47], (2) perceived risk of harm from use, and (3) self-efficacy to refuse alcohol.

**Table 2 table2:** Adolescent participant study assessment measures by data collection time point across 12 months in the Adolescent Substance Use Prevention Intervention Research (ASPIRE) multisite cluster randomized controlled trial.

Measure					Data collection time point																								
					Eligibility survey			Previsit survey			CRAFFT-IS^a^			Postvisit survey			Monthly^b^			3 mo			6 mo			9 mo			12 mo

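### The 888/1268/1300 sample-size chain makes no allowance for riding-risk-only participants, so on the article's own rates the primary analysis would have about 828 retained drinkers rather than 888

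*Protocol article*

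**What the plan says.** All places are in the Protocol article.

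- **Primary analysis population (Outcome Measures; Objectives agrees).** Past 90-day HED is assessed "as reported by adolescents during the 12-month follow-up period, among adolescents who report past 12-month drinking at baseline".
- **Enrolled population (Adolescents, eligibility).** Participants must "report past 12-month alcohol use or past 12-month riding risk". A non-drinker with riding risk is therefore enrolled but is outside the primary analysis.
- **Required analysis size (Adolescents, sample size).** "a minimum analysis sample size of 888 participants with 12-month follow-up data would provide 86% power to detect an effect size of ≥20" per cent, for HED.
- **Recruitment.** "Applying the conservative estimate of 70% retention at 12 months, we need to recruit a minimum of 1268 participants".
- **Funnel.** About 4200 complete the eligibility survey, "with 1600 (40% of those screened) meeting eligibility criteria, and 1300 (80% of those eligible) enrolling".
- **Rates.** "We estimated a 37% past 12-month drinking prevalence rate, 28% riding risk prevalence rate among adolescents with past 12-month drinking", and 5.8% riding risk among non-drinkers.

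**The concern.** The only printed step from 888 to 1268 is the retention allowance. Nothing adjusts for enrolled adolescents who did not drink in the 12 months before baseline and so cannot enter the HED analysis. If 888 is the number the HED analysis needs, then 1268 and 1300 would have to be counts of drinkers. They are given as counts of all participants.

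At stake is whether the stated analysis size and power are delivered when enrolment reaches its goal. A total-enrolment target also cannot show whether the primary analysis set is on course, because the share of riding-risk-only participants may differ from the planning rates.

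**Working it through.** **Inputs (Adolescents, sample-size paragraph):** drinking prevalence 0.37; riding risk in non-drinkers 0.058; participation 0.80; retention 0.70; required analysis size 888; stated power 86%. The 28% riding risk among drinkers is not needed, because drinkers are eligible anyway. Two assumptions are added: a two-sided 5% test, since sidedness is not stated, and equal participation and retention for drinkers and riding-risk-only adolescents.

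**1. Reproduce the plan's recruitment figure.** 888 / 0.70 = 1268.6, against 1268 printed. It reproduces, and retention alone accounts for it.

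**2. Composition of the eligible pool.**
- Eligible fraction: 0.37 + 0.63 × 0.058 = 0.37 + 0.0365 = 0.4065. This agrees with the printed 40%, so the eligible pool includes riding-risk-only adolescents.
- Drinker share of those eligible: 0.37 / 0.4065 = 0.910. Riding-risk-only share: 0.090.

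**3. Retained drinkers.**

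| Enrolled | Drinkers (× 0.910) | Retained (× 0.70) | Short of 888 |
|---|---|---|---|
| 1268 | 1154 | 808 | 80 (9.0%) |
| 1300 | 1183 | 828 | 60 (6.7%) |

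For 888 retained drinkers, enrolment would have to be 888 / 0.70 / 0.910 ≈ 1394.

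**4. Power.** The 86% cannot be rebuilt independently, because no control-arm HED rate is printed. It is taken as given and scaled with the analysis size, leaving any clustering allowance unchanged: power = Φ[(1.960 + 1.080) × √(n/888) − 1.960], where 1.080 is the normal quantile for 86%.
- n = 828: Φ(3.040 × 0.9656 − 1.960) = Φ(0.976) ≈ 83.5%.
- n = 808: Φ(3.040 × 0.9539 − 1.960) = Φ(0.940) ≈ 82.6%.
- Size at which power reaches 80%: 888 × (2.802 / 3.040)² ≈ 754, where 2.802 = 1.960 + 0.842. Both figures above exceed it.

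**5. Sensitivity of the drinker share (assumed values, 1268 enrolled, 70% retained).**

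| Assumption changed | Retained drinkers | Power |
|---|---|---|
| Riding risk in non-drinkers 10% | 758 | about 80% |
| Riding risk in non-drinkers 15% | 707 | about 77% |
| Drinking prevalence 30% | 782 | about 81% |

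**6. Funnel.** 1600 / 4200 = 38%, not 40%. Applying the article's rates throughout gives 4200 × 0.4065 = 1707 eligible and 1707 × 0.80 = 1366 enrolled. Retained drinkers from 4200 screened would be 4200 × 0.37 × 0.80 × 0.70 = 870, which is also below 888.

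**The case against.** **The 86% may already be computed on the drinkers within 888.** The text says that drinking and riding-risk prevalence entered the calculation, and it labels the 888 as participants. But it also calls 888 the minimum analysis sample for the HED outcome, and riding-risk-only participants are not in that analysis. No printed step supports the subset reading. Without a control rate it cannot be excluded arithmetically, and the full calculation may sit in a document not shown.

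**The 70% retention is deliberately cautious.** At the pilot's 75%, 1300 enrolled would give 1183 × 0.75 ≈ 887 drinkers. This is true, but it uses up the safety margin that the plan says it is keeping.

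**The analysis is not confined to 12-month completers.** The Data Analysis Plan has models at 3, 6, 9 and 12 months and multiple imputation. Some information will be recovered, but the plan defines its 888 on participants with 12-month data.

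**The figures are minima and loosely rounded.** This stands. 1300 is called a minimum in the Adolescents section (and a target in the Abstract). A reader might infer that recruitment will stop at 1300, but no such rule is stated. Nor is an average of 40 patients per clinician an error: 40 clinicians is a ceiling, and about 33 completing clinicians at 40 each would give roughly 1300. At the full ceiling, 40 × 40 = 1600 enrolled would give 1600 × 0.910 × 0.70 ≈ 1019 retained drinkers.

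**Conclusion.** The point holds, at moderate severity. On its own rates the plan does not deliver the stated 888 and 86% for the primary outcome. It delivers about 828 retained drinkers and 83.5% power at 1300 enrolled, or about 808 and 82.6% at 1268.

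This rests on the printed prevalences, 70% retention, equal participation and retention in the two eligibility groups, a two-sided 5% test, and the stated 86% taken at face value.

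Two stronger readings are tempting. One is that the primary analysis is underpowered. The plan gives "With α set at ≤.05 and β at ≥.80", where the second figure evidently means power of at least 80%, and this point alone leaves power above that level; it falls below only under assumed rates well away from the printed ones. The other is that a drinkers-only requirement was relabelled as a total for everyone eligible. The printed 40% yield fits the mixed pool, and the documents do not show how the figures were assembled.

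**What to change.** 1. Restate the expected primary analysis set as about 828 retained baseline drinkers at 1300 enrolled, with power of about 83.5%, subject to any separate correction of the design effect. Say explicitly that 888 refers to drinkers, if that is what is meant.
2. Express and track the primary enrolment target as baseline past-12-month drinkers (1183 expected among 1300). Count riding-risk-only participants separately for the secondary outcome.
3. Make the funnel consistent by applying the 40.65% yield and 80% participation throughout, or mark the figures as rounded.

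**Cost:** a text change and one additional recruitment tally. Stated power falls by 2 to 3 points, and no extra patients are required. If the team prefers to keep 888 and 86%, about 1394 would need to be enrolled, which is 94 more than 1300.

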### Intervention

#### Overview

The CRAFFT-IS was developed to leverage the power of digital technology to provide a time-efficient and feasible way for busy pediatric practices to improve both the frequency and quality of adolescent substance use screening and counseling in primary care. To this end, the CRAFFT-IS consists of the following components: (1) previsit self-administered screen (CRAFFT version with extra questions that are related to nicotine vaping and tobacco use [CRAFFT 2.1+N]), immediately followed by (2) brief interactive psychoeducational content on substance use–related health risks, and (3) clinician delivery of brief MI-based counseling during the confidential portion of the well visit, guided by a computerized point-of-care decision support tool called the clinician report. In addition, as an intervention to reduce riding and driving risk, intervention clinicians provide all participating patients and their caregivers with the *Contract for Life* document [34,43]. These components are described in greater detail in the following subsections.

#### Previsit Screening

To complete the previsit self-administered substance use screening, adolescents will log in to a secure website via their smartphone (before or at visit) or a tablet computer (at visit only) and complete the CRAFFT 2.1+N, which assesses past 12-month substance use frequency, substance-related riding and driving, and signs of problematic use (eg, uses when alone) [44]. At a cut point of ≥2 *yes* answers, the CRAFFT is highly sensitive (91%) and specific (90%) for detecting SUD in adolescents [23]. The CRAFFT 2.1+N includes an item on past 12-month days of nicotine vaping and tobacco use and, if yes, an item on past 30-day use. Endorsement of past 30-day nicotine vaping or tobacco use is followed by the Hooked on Nicotine Checklist (HONC), a well-validated 10-item screen for detecting loss of autonomy over nicotine use in adolescents [45]. This study will use a modified HONC that incorporates nicotine vaping.

After completing the substance use screen, adolescents will be asked to choose up to 3 personal values from a prespecified list of 14 values (eg, creativity, family, honesty, and wealth), with the option to write in their own. The selected values are presented in the clinician report to support clinician-patient rapport building and patient-centered MI-based counseling.

#### Previsit Psychoeducation

Next, adolescents view brief interactive psychoeducational web pages on the health risks of substance use. These web pages illustrate the unique vulnerability of adolescents to the health harms of substance use through the presentation of scientific evidence and true-life stories of adolescents. We developed this content based on input from focus groups of youth who reported that this type of information was compelling [31]. For this study, the content was updated to include information about the health risks of nocotine vaping.

#### Clinician Report and Brief Counseling Protocol

The clinician report is a web-based dashboard designed to help clinicians efficiently view their adolescent patients’ responses to the substance use screening and values items and deliver brief counseling tailored to the responses. On the basis of the screening responses, counseling guidance is tailored to 1 of three substance use profiles: (1) *recent use* (use of alcohol, cannabis, or another drug in the past 3 months or use of tobacco or nicotine in the past 30 days), (2) *distant use* (use of any substance in the past 12 months but not in the past 3 months or past 30 days for nicotine vaping and tobacco), and (3) *riding risk* (no past 12-month substance use but past 12-month riding in a vehicle with a driver who was substance impaired).

The brief counseling protocol is a modified form of the brief negotiated interview, a structured MI-based counseling intervention originally developed for use in emergency departments and found to be efficacious in reducing substance use in adolescents [46]. The counseling protocol is designed for delivery in 5 to 10 minutes, depending on the severity of risk. Counseling steps are summarized in Table 1.

**Table 1 table1:** Overview of the Adolescent Substance Use Prevention Intervention Research (ASPIRE) multisite cluster randomized controlled trial’s brief counseling protocol, which is delivered by intervention clinicians to participating adolescent patients who present for a well visit and report past 12-month alcohol use, past 12-month riding risk, or both.

Counseling protocol steps	Recent use^a^	Distant use^b^	Riding risk^c^
1. Engage and build rapport	✓	✓	✓
2. Review screening results and assess further	✓	✓	✓
3. Consider pros and cons of substance use (decisional balance)	✓		
4. Discuss health risks of substance use and riding risk	✓	✓	✓
5. Evaluate readiness to change substance use (readiness ruler [47]) and reasons for change	✓		
6. Elicit next steps toward behavior change and anticipate challenges	✓	✓	✓^d^
7. Wrap up by summarizing discussion and affirming autonomy and self-efficacy	✓^d^	✓^d^	✓

^a^Patient reports past 3-month substance use. Patient may or may not report past 12-month riding with a driver who was substance impaired.

^b^Patient reports past 12-month substance use but no past 3-month use. Patient may or may not report past 12-month riding with a driver who was substance impaired.

^c^Patient reports past 12-month riding with a driver who was substance impaired and no past 12-month substance use.

^d^Clinician provides patient with the *Contract for Life* [43].

*Recent use* counseling uses the MI style of communication to elicit the adolescent’s reasons for and problems with substance use. The clinician discusses the adolescent’s values, shares health information, explores the adolescent’s reasons for and readiness to change their substance use behavior using a readiness ruler [47], and guides the adolescent through planning behavior change. The counseling concludes by summarizing the discussion and affirming the adolescent’s autonomy and self-efficacy. *Distant use* counseling involves affirming and supporting the adolescent’s continued nonuse, discussing health risks associated with past substance use, and anticipating and planning for challenges with maintaining abstinence. *Riding risk* counseling also includes affirmation and support of the adolescent’s continued nonuse, discussion of health risks associated with riding with a driver who is substance impaired, and counseling to identify and plan safe transportation at all times. Both the *distant use* and *riding risk* counseling protocols are guided in a structured step-by-step manner similar to *recent use* counseling.

Near the end of the brief tailored counseling, intervention clinicians provide *all* participating patients with a paper or electronic version of the *Contract for Life*. Developed by Students Against Destructive Decisions, the *Contract for Life* asks youth and their caregivers to develop and commit to a plan to ensure that adolescents always have a safe ride home with a sober driver [43].

#### Intervention Training and Fidelity Monitoring

Two clinicians with expertise in MI train intervention clinicians to deliver the intervention counseling. Training was initially structured as 5 self-study modules on a web-based learning platform and 5 live sessions with expert trainers (approximately 7 total training hours). As scheduling the 5 live sessions was found to be challenging with the first practice, the study team restructured the training to include longer self-paced asynchronous modules to reduce scheduling challenges without changing the total number of training hours. The updated training schedule consists of 5 self-study modules with recorded lectures, 2 live counseling practice sessions, and 1 live technical training session to orient clinicians to the clinician report and tablet computers.

The self-study modules include video-recorded presentations on MI-based counseling principles, the counseling steps for each of the 3 risk categories, video-recorded mock counseling demonstrations with accompanying annotated transcripts, and self-assessment questions. In the 2 live sessions, the expert trainers guide clinicians through case-based practice of the counseling steps and provide feedback.

To establish baseline competency, each clinician completes the counseling steps with a standardized patient for each of the 3 risk categories in a single recorded videoconference session. The trainers and 2 research staff members review these recordings using a standardized rating form. The trainers then meet with each clinician for individualized feedback and coaching. For fidelity monitoring, clinicians complete mock counseling sessions and receive feedback quarterly. In addition, the intervention trainers host optional live videoconference sessions (*office hours*) every 1 to 2 months for extra coaching.

#### Intervention Modification or Discontinuation

No concomitant care and interventions are prohibited during the trial beyond those defined in the practice inclusion criteria. We will withdraw a participant from the study if there is evidence to suggest that continuing in the study may be inappropriate (ie, there are intervening medical, mental health, or social circumstances that preclude or disrupt participation). Data collected from withdrawn participants will still be used in the analysis.

### Outcomes and Measures

#### Study Activities and Assessment Timeline

Figure 1 illustrates the chronology of participating clinician and adolescent study activities.

**Figure 1 figure1:**
[figure not shown]
Chronological overview of clinician and adolescent milestones during the Adolescent Substance Use Prevention Intervention Research (ASPIRE) multisite cluster randomized trial. CRAFFT: Car, Relax, Alone, Forget, Family/Friends, Trouble.

#### Outcome Measures

A detailed listing of study outcome measures, their reference sources where applicable, and time points of data collection is presented in Table 2, and thus they are only briefly described here. These measures are also reported in the ClinicalTrials.gov registry.

Our primary outcome measure is past 90-day HED, as reported by adolescents during the 12-month follow-up period, among adolescents who report past 12-month drinking at baseline. HED is defined using the age- and sex-specific cut points recommended by the NIAAA: ≥3 drinks on a single occasion for youth assigned female at birth who are aged 14 to 17 years, ≥4 drinks for youth assigned male at birth who are aged 14 to 15 years, and ≥5 drinks for youth assigned male at birth who are aged 16 to 17 years [68]. Our secondary outcome measure is any past 90-day riding with a driver who was substance impaired (who used alcohol, cannabis, or another drug) or driving while substance impaired. The exploratory outcomes of interest include past 90-day days of use of other commonly used substances among adolescents (ie, nicotine and cannabis) and experience of negative consequences associated with alcohol use (eg, missing school or work and getting into trouble at school, home, or work). In addition, we will explore the following intermediate outcome measures as hypothesized effect mediators: (1) report of readiness to reduce or stop alcohol use using a readiness ruler [47], (2) perceived risk of harm from use, and (3) self-efficacy to refuse alcohol.

**Table 2 table2:** Adolescent participant study assessment measures by data collection time point across 12 months in the Adolescent Substance Use Prevention Intervention Research (ASPIRE) multisite cluster randomized controlled trial.

Measure					Data collection time point																								
					Eligibility survey			Previsit survey			CRAFFT-IS^a^			Postvisit survey			Monthly^b^			3 mo			6 mo			9 mo			12 mo
